#### The Pittsburgh sleep quality index

PSQI is a self-reported outcome measure that assesses sleep quality and usual sleep habits. The recall frame is 1 month, and the outcome measure consists of 24 individual items measuring seven dimensions and categorized into sleep efficiency factors (sleep quality, sleep latency, sleep duration, and habitual sleep efficiency) and sleep disturbance factors (sleep disturbance, use of sleep medications, and daytime disturbance) [33].

#### Health literacy questionnaire

The Health Literacy Questionnaire (HLQ) has nine scales that each measure an aspect of the multidimensional construct of health literacy [34]. Low health literacy has been reported to be associated with increased mortality, hospitalization, lower use of preventive healthcare services, difficulty communicating with health professionals, and poorer knowledge about disease processes and self-management skills among people with chronic conditions such as heart disease. The HLQ is used in many settings, including the development of interventions, and for evaluation of health programmes [35–38].

#### Impact of event scale-revised

The IES-R is a 22-item patient-reported outcome measure that assesses subjective distress caused by traumatic events [39]. The scale is rated on a 0 (not at all) to 4 (extremely) scale with respect to how distressing each item has been during the past week. Three subscales are formed and reflect intrusion (eight items), avoidance (eight items), and hyperarousal (six items).

#### Adverse events

During the trial period, serious adverse events, adverse events, and adherence will be registered. A serious adverse event is defined as an event that leads to either death, hospitalization, or a serious risk of deterioration in health, and all other reported adverse events such as pain, fatigue, and oedema are defined as non-serious adverse. Harms will be evaluated by calculating the relative risk (RR), separately for serious and nonserious adverse event between the intervention and control group.

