### Intervention

Individuals allocated to the intervention group will in addition to the usual care group receive a comprehensive tailored rehabilitation intervention focusing on supporting RTW.

The intervention is based on a multidisciplinary rehabilitation team approach (psychologists, physiotherapists, social workers, physicians within social medicine and occupational medicine, and psychiatrists). A comprehensive neurocognitive assessment and a thorough individual assessment of rehabilitation needs will be conducted to inform the individually tailored intervention plan. The plan will be developed, discussed, and planned at multidisciplinary rehabilitation team conferences. Ongoing monthly evaluation and possible adjustments of the rehabilitation plan are further discussed at multidisciplinary rehabilitation team conferences. The intervention is designed as a pragmatic individually tailored rehabilitation intervention; hence, the content and the delivery of the rehabilitation will not be uniform but based on individual needs. Therefore, based on the individual rehabilitation plan, a participant can be offered interventions that target the individual needs without limitations in relation to frequency and intensity but with a limit in relation to duration (up until 12 months after the cardiac arrest). Core intervention elements are as follows: (1) comprehensive assessment of individual rehabilitation needs including neuropsychology tests in order to make an individually tailored intervention plan coordinated with the multidisciplinary rehabilitation team; (2) providing strategies to lessen impact for the individual cognitive impairment; (3) educating survivors and relatives about the impact of a cardiac arrest and consequences on daily life; (4) work preparation, including establishment of routines and opportunities to practice work skills; (5) collaboration with the local municipality’s job centre and employers to plan, support, and monitor graded RTW; and (6) short-term therapy by psychologist dealing with thoughts and behaviour in relation to cardiac arrest. Core elements and reference activities in the intervention related to timing are presented in Fig. 1.

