### Secondary outcomes

All secondary outcomes: readiness for return-to-work (RRTW), Multidimensional Fatigue Inventory (MFI-20), The 5-level EuroQol 5-domain (EQ-5D-5L) quality-of-life questionnaire, European quality-of-life survey (HeartQoL), the Pittsburgh Sleep Quality Index (PSQI), Health Literacy Questionnaire (HLQ), and Impact of Event Scale-Revised (IES-R), modified job descriptions and job task, and adverse events will be collected within the first 12 weeks after hospital discharge. There will be at least one interim test at 26 weeks and again at the primary end point at 52 weeks. Please see assessment timeline in Table 1.

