#### Multidimensional fatigue inventory

Fatigue is a very commonly reported symptom in sudden cardiac arrest survivors. To measure the level of fatigue, and change over time, the 20-item patient-reported outcome measure MFI-20 was chosen. MFI-20 consist of five fatigue scales covering the following: general fatigue, physical fatigue, reduced activity, reduced motivation, and mental fatigue [23].

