### Recruitment, assignment of interventions, sequence generation, and allocation concealment

We will recruit trial participants directly from the cardiology ward. A study nurse at the ward will approach eligible survivors and invite them to participate in the present study. Participants will be randomly assigned to either the intervention or the usual care group using a computer random generator, with a 1:1 allocation by using varying block sizes. The randomisation will be conducted using the RedCap randomization module and will be stratified on sex (M/F) and age. Allocation concealment will be ensured as the randomization module block sizes are unknown, and the allocation will be locked after randomization. Clinical staff at the departments will obtain informed consent and enroll the participants. A named study author ([name], [name], or [name]) will randomize participants, and the clinical staff at the departments will inform the participants about the allocation and start the intervention based on standard operating procedures. The CONSORT flow diagram is presented in Fig. 2.

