### Blinding

Due to the nature of the intervention, neither participants, outcome assessors, nor staff conducting the intervention can be blinded to allocation. Group allocation will be anonymized before the data will be analysed by the data analysis responsible investigator to ensure blinding.

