### Sample size

The sample size calculation for the present trial is based on a study by Moulaert et al. who evaluated the effectiveness of a rehabilitation intervention on health-related quality of life for OHCA survivors but reported exploratory finding for RTW after 1 year. In that study, 71% of the control group had returned to work after 1 year. We expect the intervention to increase this by 25% corresponding to a RTW rate of 88.8%. Using the formula for large-sample tests for proportions in a two-sample parallel design with a superiority margin of 10% and a power of 80%, 85 survivors are needed in each arm, 170 in total. Based on the sample size calculation and an expected 20% dropout rate, 107 OHCA survivors are needed in each study arm, 214 in total [42].

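### The single pooled relative risk for non-serious adverse events counts fatigue, a common symptom of the disease and also a secondary outcome, so it is hard to read as a measure of harm

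*Protocol article*

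**What the plan says.** Three places in the protocol article bear on this point.

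- **Adverse events.** Serious events are those leading to death, hospitalisation or a serious risk of deterioration. The remainder form one class: "all other reported adverse events such as pain, fatigue, and oedema are defined as non-serious adverse". The analysis follows directly: "Harms will be evaluated by calculating the relative risk (RR), separately for serious and nonserious adverse event between the intervention and control group". This gives two relative risks, one for each class.
- **Multidimensional fatigue inventory.** "Fatigue is a very commonly reported symptom in sudden cardiac arrest survivors". No percentage is given.
- **Secondary outcomes.** Fatigue is scored as an outcome in the list that opens with "All secondary outcomes: readiness for return-to-work (RRTW), Multidimensional Fatigue Inventory (MFI-20"). Adverse events are in the same list, with collection in the first 12 weeks after discharge and again at 26 and 52 weeks.

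Two features of the design affect how events come to be reported. Under Blinding, "neither participants, outcome assessors, nor staff conducting the intervention can be blinded to allocation". Under Intervention, the plan of each participant is reviewed monthly and treatment is offered "without limitations in relation to frequency and intensity but with a limit in relation to duration".

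**The concern.** A harm measure should respond to events that the intervention may cause. Here the intervention draws on graded exercise therapy and a graded return to work, so pain and overexertion are plausible harms. Those events enter the same count as fatigue, which many participants in either arm may report because of the arrest itself. The pooled RR then mixes three things: events due to rehabilitation, background symptoms of the disease, and any effect of the intervention on fatigue, which the MFI-20 is meant to measure.

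At stake is the published statement on non-serious harm. A pooled RR near 1 could conceal a clear increase in pain. An RR above 1 could reflect only more contact and fuller reporting. An RR below 1 could be a benefit on fatigue outweighing a harm elsewhere. The pooled figure alone cannot separate these.

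**Working it through.** The article states no adverse-event rate, no expected RR and no power for harms, so there is no figure of its own to reproduce. What follows shows how the stated measure behaves under assumed rates.

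**Inputs**

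- From the article: 1:1 allocation, one RR for all non-serious events, fatigue included. The sample size section gives 85 per arm, raised for dropout to 85 / (1 − 0.20) = 106.25, that is 107 per arm.
- Assumed: *h*, the risk of any other non-serious event, is 10% in control and 20% in intervention (true RR 2.0). *b*, the risk of a recorded fatigue event, is varied from 20% to 90%. The two are independent. The RR compares participants with at least one event.

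**Formula**

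P(any non-serious event) = 1 − (1 − *b*)(1 − *h*), and the pooled RR is the intervention value over the control value.

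**Case 1: equal background, equal reporting**

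| *b* | Control | Intervention | Pooled RR |
|---|---|---|---|
| 0% | 10% | 20% | 2.00 |
| 20% | 28% | 36% | 1.29 |
| 40% | 46% | 52% | 1.13 |
| 60% | 64% | 68% | 1.06 |
| 70% | 73% | 76% | 1.04 |
| 90% | 91% | 92% | 1.01 |

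Example at 60%: control 1 − 0.4 × 0.9 = 0.64; intervention 1 − 0.4 × 0.8 = 0.68; 0.68 / 0.64 = 1.06. There is also a ceiling, since the RR cannot exceed 1 / control risk. At *b* = 70% that is 1 / 0.73 = 1.37.

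**Case 2: fuller reporting in the intervention arm**

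Take *b* = 70%, with 50% of fatigue recorded in control and 80% in intervention. Recorded fatigue is 0.70 × 0.50 = 35% and 0.70 × 0.80 = 56%.

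- No true harm (*h* = 10% in both arms): control 1 − 0.65 × 0.9 = 0.415; intervention 1 − 0.44 × 0.9 = 0.604; RR 1.46.
- With the assumed harm: intervention 1 − 0.44 × 0.8 = 0.648; RR 0.648 / 0.415 = 1.56.

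With a smaller gap in recording (70% v 90%) and no harm, the RR is 0.667 / 0.541 = 1.23.

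**Case 3: the intervention relieves fatigue**

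Let fatigue be 70% in control and 60% in intervention, with the assumed harm present. Control 1 − 0.3 × 0.9 = 0.73; intervention 1 − 0.4 × 0.8 = 0.68; RR 0.93. A doubling of other events appears as a reduction.

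**What separate rows would show**

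In cases 1 and 3 the RR without fatigue is 0.20 / 0.10 = 2.00. In case 3 the fatigue row is 0.60 / 0.70 = 0.86. In case 2 without harm, the RR without fatigue is 0.10 / 0.10 = 1.00 and the fatigue row is 0.56 / 0.35 = 1.60. Separate rows show where a difference lies, but they do not remove unequal reporting; only eliciting events alike in both arms addresses that.

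**The case against.** The strongest reply is that the sentence on non-serious events only sorts events by seriousness. A symptom must first qualify as an adverse event, and the rules for onset, coding and tables by type may stand in the full protocol or in the analysis plan that the article promises. That is right as far as it goes: their absence from an article is no fault, and the text does not say that fatigue present since the arrest counts. What remains is what the article does fix, namely one RR for the class and fatigue named in it. A stricter onset rule would lower *b*, but even at 20% an RR of 2.0 becomes 1.29.

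Several stronger readings are tempting and are not supported.

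- **That fatigue is near-universal, so most participants will have an event.** The article says it is very common and gives no rate.
- **That the RR must be pulled towards 1.** This needs equal background and equal reporting. Cases 2 and 3 show inflation and reversal.
- **That the safety assessment as a whole is unreliable.** Serious events have their own RR, which this leaves untouched.
- **That fatigue is wrongly counted twice.** A scale score and an event report are different measures, and both may be kept.
- **That fatigue should be left to the MFI-20 alone.** Worsened fatigue is itself a plausible harm of graded exercise, and a mean score can miss worsening in individuals.
- **That the trial loses power to detect harm.** The article plans an estimate and states no test of harms. If a two-sided 5% comparison were made, power in the example at 107 per arm would fall from 54% without fatigue to 9% at 60% background. At 85 per arm it would be 45% even without fatigue, so the fix would not make the comparison well powered.

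**Conclusion.** The point holds for the non-serious RR only. As stated, that measure pools a common symptom of the disease, which is also a secondary outcome, with events that rehabilitation may cause. The result can be diluted, inflated or reversed, and the direction cannot be known in advance. In the assumed example an RR of 2.0 for other events becomes 1.29 to 1.01 for background fatigue of 20% to 90%, 1.56 with fuller reporting in the intervention arm (1.46 with no harm at all), and 0.93 with a benefit on fatigue.

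These figures rest on assumed event rates, independence of fatigue and other events, and an RR based on participants with at least one event. They show the possible size of the problem and do not predict the result of the trial. The change is worth making because it is cheap and the article already commits to the measure.

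**What to change.** In the section on adverse events:

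1. Count as non-serious adverse events only those that are new or worse since randomisation.
2. Elicit them with the same questions in both arms, at the timepoints already listed under Secondary outcomes.
3. Report the RR by event type (pain, fatigue, oedema, other) beside the pooled RR, and show the pooled RR with and without fatigue. Keep worsened fatigue as its own row.

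The cost is a change of wording and a few more table rows, with fewer counted events in each row and so wider intervals. The assessment timepoints already exist. Recruitment began in February 2022, so onset or worsening may not have been recorded for participants already enrolled. If so, apply the first two items from the date of the change, say so in the report, and give the rows by type for all participants as far as event type was recorded.

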## Background

Each year, more than 5000 citizens experience an out-of-hospital cardiac arrest (OHCA) in Denmark. In 2021, the Danish 30-day survival rate was 13% equivalent to yearly incidence of 610 OCHA survivors [1].

Rehabilitation targeting physical, neurological, and psychological consequence after OHCA is recommended in international clinical guidelines. Due to hypoxic–ischaemic brain injury, the course of acute post-cardiac arrest care and the trauma of resuscitation the frequency of cognitive impairment and emotional reactions are high in survivors of cardiac arrest. These problems affect survivors and restrict their ability to return-to-work (RTW) [2, 3]. Although the majority of cardiac arrest survivors are classified with mild to moderate cognitive impairment, roughly 50% experience long-term neurocognitive impairment. Thus, most cognitive recovery is found to occur during the first 3 months after resuscitation [4, 5]. Looking at emotional issues, both depression, anxiety, and post-traumatic stress disorder are found to affect approximately 20–25% of survivors in the long term [6]. Overall, these neuropsychological postarrest challenges complicate participation in society and are associated with social issues such as failure to resume social activities and impaired RTW [3, 6, 7]. A Danish nationwide cohort study by Jørgensen and colleagues investigated RTW and the subsequent detachment from employment in cardiac populations [8]. The authors found high probabilities of not returning to work, in patients diagnosed with heart failure. These results are in line with our previous findings [2]. Six months after resuscitation, we found 58% of survivors on full-time sick leave or working notable less (10 h/week) compared to prior to the cardiac arrest. In addition, an extensive part of those who had RTW had changed job descriptions or had been assigned less demanding job tasks. Other resuscitation research support these findings, as they found that flexible work hours and/or modified job descriptions were offered to 74% of participants in a register-based OHCA population [9].

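### The relative risk for non-serious adverse events is not restricted to events collected the same way in both arms, so denser trial contact in the intervention arm could inflate it

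*Protocol article*

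**What the plan says.** **Registration and analysis (Adverse events).** The collection window is the whole study: "During the trial period, serious adverse events, adverse events, and adherence will be registered". Serious events are defined thus: "A serious adverse event is defined as an event that leads to either death, hospitalization, or a serious risk of deterioration in health". The remainder are a residual class of what is reported: "all other reported adverse events such as pain, fatigue, and oedema are defined as non-serious adverse". The comparison is then fixed: "Harms will be evaluated by calculating the relative risk (RR), separately for serious and nonserious adverse event between the intervention and control group".

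**Scheduled collection (Secondary outcomes; Table 1 footnote).** Adverse events are in the list of outcomes collected within 12 weeks of discharge, with no restriction to one arm. After that, "There will be at least one interim test at 26 weeks and again at the primary end point at 52 weeks". The Table 1 footnote gives the assessment times as 2, 6, 12, 26 and 52 weeks.

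**Contact with staff.** The Intervention section offers a multidisciplinary programme, not capped in frequency or intensity, until 12 months after the arrest. It adds: "Ongoing monthly evaluation and possible adjustments of the rehabilitation plan are further discussed at multidisciplinary rehabilitation team conferences". Under Usual care, participants see an occupational therapist if the MoCA score is 26 or lower, and have municipal rehabilitation if referred. Under Relevant concomitant care and interventions, hospital follow-up and social worker consultations continue in both arms.

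**Blinding.** "neither participants, outcome assessors, nor staff conducting the intervention can be blinded to allocation". Only the analyst is masked.

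**The concern.** A between-arm relative risk measures harm only if an event of a given kind has about the same chance of being recorded in either arm. For reported symptoms, that chance depends on how often someone is there to hear the report. Intervention participants can mention pain or fatigue at any rehabilitation session. For usual care, the trial contacts described are the scheduled assessments. After week 12 these leave gaps of 14 weeks (12 to 26) and 26 weeks (26 to 52), to be covered by recall. The Background says of survivors in general that "roughly 50% experience long-term neurocognitive impairment".

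At stake is how the harms result is read. A harmless programme could show an excess of non-serious events. A real excess could be put down to reporting, because the stated analysis cannot separate the two. Masking the analyst does not repair counts that were unequal when collected. The internal committee that discusses safety data monthly (Data monitoring) would see the same counts.

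**Working it through.** The protocol gives no harm rate, expected relative risk or power for harms, so there is no figure to reproduce. The check has three steps.

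**1. Does the text keep the comparison symmetric?**

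- A common collection frame exists (Secondary outcomes).
- The Adverse events section does not tie the relative risk to that frame. It registers events throughout the trial.
- No section says that events noted at rehabilitation sessions enter the ratio, and none says that they stay out.
- Monthly safety discussion suggests that events may arrive between assessments. Staggered enrolment would also supply new data each month, so this is weak support.

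The asymmetry is therefore permitted, not prescribed.

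**2. How large could the distortion be?**

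Inputs:

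- n = 107 per arm randomized, and 85 before the allowance for dropout (Sample size).
- Assumed, because the document gives neither: true 12-month risk r of 20%, 40% or 60%, equal in both arms; capture d_I = 90% with intervention and d_C = 75% or 60% with usual care.
- The relative risk is taken to count people with at least one recorded event.

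Apparent RR = (r × d_I)/(r × d_C) = d_I/d_C, whatever the value of r:

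- 0.90/0.75 = 1.20
- 0.90/0.60 = 1.50
- equal capture: 1.00

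The chance that a 95% interval lies wholly above 1 is Φ(ln RR/SE − 1.96). Here SE = √[(1−p_I)/(n p_I) + (1−p_C)/(n p_C)], p_I = r × d_I and p_C = r × d_C.

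Example with r = 40%, 90% against 60%, n = 107: p_I = 0.36 and p_C = 0.24. SE = √(0.64/38.52 + 0.76/25.68) = √(0.0166 + 0.0296) = 0.215. ln 1.5 = 0.405, and 0.405/0.215 − 1.96 ≈ −0.07, which gives 47.1%.

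| Capture | n per arm | RR | r = 20% | r = 40% | r = 60% |
|---|---|---|---|---|---|
| 90% vs 90% | 107 | 1.00 | 2.5% | 2.5% | 2.5% |
| 90% vs 75% | 107 | 1.20 | 8.5% | 15.2% | 25.8% |
| 90% vs 60% | 107 | 1.50 | 22.9% | 47.1% | 73.4% |
| 90% vs 60% | 85 | 1.50 | 19.1% | 39.0% | 63.5% |

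The protocol states no significance test for harms. These percentages show what a reader would see if a 95% interval were put around the ratio. They are not the error rate of a planned test. The chance rises with the true risk, so common symptoms are the most exposed. The section on the Multidimensional Fatigue Inventory describes fatigue as very common in this population.

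**3. What if a symptom persists and can be picked up more than once?**

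With k independent chances, capture is 1 − (1 − d)^k:

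- k = 2, 90% vs 60%: 0.990/0.840 = 1.18. 90% vs 75%: 0.990/0.9375 = 1.06.
- k = 3, 90% vs 60%: 0.999/0.936 = 1.07. 90% vs 75%: 0.999/0.984 = 1.01.

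Independence is also an assumption. The distortion is largest for brief, resolved events and shrinks for persistent symptoms.

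**The case against.** The strongest reply is that the schedule already collects adverse events in both arms, and that how events are elicited belongs in the full protocol, the analysis plan or the standard operating procedures, none of which is shown. This stands in part. Missing detail about elicitation is no fault of the article, and the common schedule lowers the risk. But the article does fix the comparison, and as worded it admits events from any source.

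A reader might infer that only the intervention arm has ongoing contact with staff. The documents do not support that. Usual care includes occupational therapy or municipal rehabilitation for some, and hospital follow-up and social worker consultations continue in both arms. The contrast is confined to the trial rehabilitation team. Nor is the monthly evaluation an extra visit or a safety enquiry: it is discussed at team conferences. The programme is offered according to need, so not every intervention participant is seen often.

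A reader might also infer that both relative risks are compromised. Death and hospitalization depend little on how often trial staff meet the participant, and the two ratios are computed separately.

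Three further points stand. The impairment figure describes survivors generally, whereas the trial enrols people able to understand and complete its surveys. The direction is likely but not certain, since unblinded intervention staff could also under-report. And a restricted ratio still relies on recall over the long gaps. That makes the comparison more even, not more complete, which is why the all-source count should be kept beside it.

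**Conclusion.** The concern holds in limited form. As written, the relative risk for non-serious events, and the part of the serious-event ratio that rests on a judged risk of deterioration, can be inflated by unequal detection. Death and hospitalization are little affected.

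This is a plausible risk and not a demonstrated bias. On assumed capture of 90% against 60-75% and equal true risk, the apparent relative risk is about 1.2-1.5 for events with a single chance of being recorded. It falls to about 1.06-1.18 with two chances and 1.01-1.07 with three. It would be wrong to infer from this that the trial will report a false harm signal: every capture rate is an assumption, and no harms test is stated. The point is worth acting on because an even comparison is available on the existing schedule at little cost.

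**What to change.** In the Adverse events section:

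- Base the main relative risk for non-serious events on events elicited by the same standard question at the assessments common to both arms. Name those assessments, drawing on Secondary outcomes and Table 1.
- Record in REDCap the source of each event (scheduled question, rehabilitation session or other).
- Report the all-source relative risk for non-serious events, and the count of events noted only in sessions, as supplementary results.
- Keep the serious-event relative risk on all sources. Show deaths and hospitalizations separately from events classed as a serious risk of deterioration.

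The cost is a few sentences and one data field, with no new visits. The downside is small: non-serious events noted only in intervention sessions leave the main ratio, although they are still reported. The change should be registered as an amendment before the data are analysed.
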